### 3.5 Participant timeline

| Study period       | Enrolment | Randomization | Intervention | Day 5   | 6-8 weeks | 6 months   |
|--------------------|-----------|---------------|--------------|---------|-----------|------------|
| Time point         | Day -3~0  |               | Day 1        | Day 5±2 | Day 49±10 | Day 180±30 |
| Eligibility screen | •         |               |              |         |           |            |
| Informed consent   | •         |               |              |         |           |            |
| Demographics       | •         |               |              |         |           |            |
| Randomization      |           | •             |              |         |           |            |
| Intervention       |           |               | •            |         |           |            |
| echocardiography   |           |               |              | •       | •         | •          |
| Body temperature   | •         |               |              | •       | •         |            |
| CBC/DC             | •         |               |              | •       | •         |            |
| GOT/GPT            | •         |               |              | •       | •         |            |
| CRP                | •         |               |              | •       | •         |            |
| AE、SAE             |           |               | •            | •       | •         |            |
|                    |           |               |              |         |           |            |

### 3.6 Sample size

The sample size determination is based on the result of our retrospective data.[16] The estimated proportions of CAL are 17% after IVIG and high-dose aspirin combination treatment and 15.4% after IVIG alone treatment. We consider the difference less than 10% is of no clinical importance. The following contents are the statistical basis for estimating sample size for this trial.

$$H_0: P_T - P_S \leq \delta$$

$$H_A: P_T - P_S > \delta$$

$$P_T: \text{CAL-free rate in test group} = 0.846$$

$$P_S: \text{CAL-free rate in standard group} = 0.83$$

$$\delta = -0.1$$

Assume that the type I and type II error rates are  $\alpha = 0.05$ ,  $\beta = 0.2$ , respectively. The clinically meaningful difference  $\delta$  is -0.1. The CAL-free rate of test group (IVIG alone)  $P_T$  is 0.846 and that of standard group (IVIG + high dose aspirin)  $P_S$  is 0.83.

Assume the sample sizes of two groups are equal, the sample size of each group for the non-inferiority trial is 125 patients. Offsetting a maximal dropout of 10%, 139 patients are required for per group. That is, a total sample size of 278 patients is required for the trial.

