## **Withdraw criteria**

Participants should be withdrawn from the clinical trial if any of the conditions set below has occurred. The reason for a patient withdrawn from the study will be recorded in the case report form (CRF) and in the participant's medical record.

1. Participant or his/her legal guardian decides to withdraw his/her ICF.
2. Participant has allergic reaction during IVIG or aspirin treatment.
3. Participant develops AE or SAE that the investigator considered a cessation of the study treatment is necessary.
4. Participant is lost of follow up.
5. Investigator considers that the participant is no longer physically and/or psychologically feasible to remain in the study.

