### **Appendix B: Case Report Form**

### **Appendix C: Common Terminology Criteria for Adverse Events (CTCAE) version**

**4.03. (A complete copy of the CTCAE version 4.03 will be held in each site study file)**

## **Statistical analysis**

All of the baseline characteristics are used to study the comparability of both trial arms. The primary outcome evaluation and safety evaluation are carried out on the intention-to-treat (ITT) population. Continuous variables will be described using either the mean (standard deviation) or median (interquartile range), as appropriate, and categorical variables will use count (percentage). Participants' characteristics are compared using a  $\chi^2$  test for categorical variables and a t-test or Wilcoxon rank sum test for continuous variables.  $P$ -values < 0.05 are considered statistically significant.

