**Day 5 follow up Visit**  
**(Visit 4, Day 3 to 7)**

**Day 5 follow up laboratory data date:** 20□□/□□/□□ (yyyy/mm/dd)

| Item | Value | Unit       | Item       | Value | Unit    | Item       | Value | Unit |
|------|-------|------------|------------|-------|---------|------------|-------|------|
| WBC  |       | 1000/ul    | MCHC       |       | gHb/dl  | Monocyte   |       | %    |
| RBC  |       | Million/ul | RDW-SD     |       | %       | Eosinophil |       | %    |
| HGB  |       | g/dl       | RDW-CV     |       | %       | Basophil   |       | %    |
| HCT  |       | %          | PLT        |       | 1000/ul | AST/GOT    |       | U/L  |
| MCV  |       | fL         | Segment    |       | %       | ALT/GPT    |       | U/L  |
| MCH  |       | pg/cell    | Lymphocyte |       | %       | CRP        |       | mg/L |

**Day 5 follow up 2D echocardiography date:** 20□□/□□/□□ (yyyy/mm/dd)

Performer: \_\_\_\_\_

Body weight: □□.□ Kg

Body height: □□□.□ cm

LMCA: \_\_\_\_\_mm, Z score: \_\_\_\_\_

LAD: \_\_\_\_\_mm, Z score: \_\_\_\_\_

RCA: \_\_\_\_\_mm, Z score: \_\_\_\_\_

Coronary artery lesion: ☐Yes ☐No

Lesion type: \_\_\_\_\_

**Discharge date:** 20□□/□□/□□ (yyyy/mm/dd)

[figure not shown]

|                                                                                                                                                   |                                 |             |
|---------------------------------------------------------------------------------------------------------------------------------------------------|---------------------------------|-------------|
| I have reviewed all data recorded on all pages of this visit and certify that they are accurate, complete and consistent to the subject's record. | Investigator's Signature | Date |
|                                                                                                                                                   |                                 |             |

**Week 6-8 follow up Visit  
(Visit 5, Day 39 to 59)**

**Week 6-8 follow up laboratory data date:** 20□□/□□/□□ (yyyy/mm/dd)

| Item | Value | Unit       | Item       | Value | Unit    | Item       | Value | Unit |
|------|-------|------------|------------|-------|---------|------------|-------|------|
| WBC  |       | 1000/ul    | MCHC       |       | gHb/dl  | Monocyte   |       | %    |
| RBC  |       | Million/ul | RDW-SD     |       | %       | Eosinophil |       | %    |

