**Month 6 follow up Visit**  
**(Visit 6, Day 150 to 210)**

**Month 6 follow up 2D echocardiography date:** 20□□/□□/□□ (yyyy/mm/dd)

Performer: \_\_\_\_\_

Body weight: □□.□ Kg

Body height: □□□.□ cm

LMCA: \_\_\_\_\_mm, Z score: \_\_\_\_\_

LAD: \_\_\_\_\_mm, Z score: \_\_\_\_\_

RCA: \_\_\_\_\_mm, Z score: \_\_\_\_\_

[figure not shown]

Coronary artery lesion: ☐Yes ☐No

Lesion type: \_\_\_\_\_

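### The plan meets missing 6-8 week echoes only by enrolling more children, so the primary comparison is in effect a completer analysis, although recorded echoes could support an all-randomised check.

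*Combined protocol and SAP*

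**What the plan says.** Protocol section 3.4 defines the primary outcome as CAL at 6-8 weeks, judged from echo Z scores of three proximal coronary segments. Section 3.6 sizes the trial at 125 per arm and then allows for loss: "Offsetting a maximal dropout of 10%, 139 patients are required for per group". The synopsis gives the purpose of the 278 as leaving 250 per-protocol children. The withdrawal criteria in section 3.2 include "Participant is lost of follow up", with no rule for the outcome of such a child.

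Section 3.11 of the protocol places the primary outcome on the per-protocol population. The separate Statistical analysis section (the SAP) differs: "The primary outcome evaluation and safety evaluation are carried out on the intention-to-treat (ITT) population". Neither text defines its set, mentions imputation, or says how a missing 6-8 week echo, or a death before it, is handled.

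The CRF in Appendix B also has echo pages before and after the primary visit, headed "Day 5 follow up 2D echocardiography date" and "Month 6 follow up 2D echocardiography date". Each records Z scores for the same three segments. The plan gives these measurements no role when the 6-8 week echo is absent.

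**The concern.** Enrolling extra children restores precision. It does nothing about bias if the children who are lost differ from those who stay. Section 3.9 says that participants and investigators know the arm, so loss could depend on both arm and coronary findings. If test-arm children with lesions are the ones who fail to return, the observed test-arm CAL rate is too low and the comparison moves toward a non-inferiority claim.

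Switching to the SAP's ITT label does not settle this. An ITT analysis needs an outcome for every randomised child, and no rule supplies one. If a rule is chosen only after the data are seen in an open-label trial, a close result will be open to challenge.

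**Working it through.** **1. Inputs (protocol section 3.6).**
- CAL rates: "The estimated proportions of CAL are 17% after IVIG and high-dose aspirin combination treatment and 15.4% after IVIG alone treatment", i.e. CAL-free 0.83 and 0.846.
- Margin: "We consider the difference less than 10% is of no clinical importance", i.e. 10 points.
- Alpha 0.05 (sidedness not stated), power 80%, equal arms, dropout at most 10%.

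**2. The plan's own figure.**
n = (z_α + z_β)² × [p_T(1 − p_T) + p_S(1 − p_S)] / (p_T − p_S + 0.10)²
= (1.645 + 0.842)² × (0.846 × 0.154 + 0.83 × 0.17) / 0.116²
= 124.7, so 125 per arm.
125/0.9 = 138.9, so 139 per arm and 278 in total.
The stated figures reproduce with one-sided 0.05. One-sided 0.025 gives 159 (177 after dropout) and does not. The dropout arithmetic is correct. It allows 139 − 125 = 14 children per arm, 28 in all, to be absent.

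**3. Test used below (assumption).** The plan names no non-inferiority test or interval. I use the unpooled Wald upper limit for the CAL difference, test minus standard:
U = d + 1.645 × √[p_t(1 − p_t)/n_t + p_s(1 − p_s)/n_s]
Non-inferiority is met if U is below 10 points. One-sided 95% matches the sample size.

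**4. A result near the margin.**

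| Test CAL | Standard CAL | Difference | SE | U (points) | Result |
|---|---|---|---|---|---|
| 25/125 | 21/125 | 3.20 | 4.90 | 11.3 | fails |
| 23/123 | 21/125 | 1.90 | 4.85 | 9.9 | passes |

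The second row is the first after two test-arm children with lesions have been lost.

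**5. About the planned result.** 125 × 0.154 ≈ 19 and 125 × 0.17 ≈ 21. Missing test-arm children are added back as CAL, to numerator and denominator.

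| Added test-arm lesions | Test CAL | U (points) | Result |
|---|---|---|---|
| 0 | 19/125 | 6.0 | passes |
| 2 | 21/127 | 7.5 | passes |
| 5 | 24/130 | 9.5 | passes |
| 6 | 25/131 | 10.2 | fails |
| 14 | 33/139 | 15.0 | fails |

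If all 14 missing standard-arm children are also counted as lesion-free, four added test-arm lesions suffice. For scale, 14 children at the planned test-arm rate would have 14 × 0.154 ≈ 2.2 lesions.

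**6. How often two children matter.** Summing exact binomial probabilities at the planned rates with 125 per arm, 9.7% of trials (12% of passes) would pass and yet be overturned by two added test-arm lesions. With both rates at 17%, the figures are 11.4% and 17%.

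**7. Sensitivity to alpha.** At one-sided 97.5%, both rows in step 4 fail (12.8 and 11.4 points), so that example does not flip. At 19 vs 21 the limit is 7.5 points and four added lesions are enough.

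**8. Size of bias (illustration only).** One scenario assumes true CAL of 27% vs 17%, test-arm loss of 25% with a Day 5 lesion and 6% without, standard-arm loss of 10%, and a correlation of 0.5 to 0.85 between Day 5 and 6-8 week Z scores. The completer difference is then roughly 1 to 3 points too small. None of these loss rates or correlations is in the documents. If 27% of test-arm children had a Day 5 lesion, loss would be 0.27 × 25 + 0.73 × 6 = 11.1%, above the plan's 10% maximum.

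**9. Loss unrelated to arm and outcome.** There is then no bias. With SE = √(0.2714/n), power is 80.1% at 125 per arm and at most 83.7% if all 139 were recovered, so the gain in precision is modest.

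**The case against.** The strongest reply is that the documents nowhere say that a child without the echo is excluded. The two texts name different populations and define neither, and an undefined ITT set could be run with missing counted as CAL. That is right: the completer analysis is an inference. It remains the natural default, because the sample is sized on per-protocol children and the ITT label supplies no outcome. The conflict between the two populations is a separate matter.

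Other readings that a reader might infer go too far:
- **Two children would overturn the expected result.** They would not; step 5 needs six. Every non-inferiority threshold has a band in which a few events decide the verdict.
- **A child with a Day 5 lesion is a missed primary event.** The endpoint is status at 6-8 weeks. The earlier trial described in section 2.1 reports new CAL of 18-19% before day 30 but prevalence of 8-10% at day 30, which suggests that many early lesions resolve.
- **The trial carries a known bias or an inflated error rate.** The scenario's inputs are undocumented and it shows one direction only. Families told of dilatation may be more likely to return, and selective loss in the standard arm would push the other way. That imputation removes the bias there is built in, because loss was made to depend on the Day 5 result.
- **Coronary deaths should simply be added to the endpoint.** That would make it a composite. Section 3.12 records adverse events until discharge, although the 3.5 timeline marks them to 6-8 weeks, and the exit form lists no death option. Such events may not be captured, and the documents give no expected number.

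Fourteen per arm is also a ceiling. Some children outside the per-protocol set may still have the echo.

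**Conclusion.** The point holds as a gap in method that is cheap to close. The plan answers missing primary outcomes with numbers alone, and nothing in it tests whether selective loss could explain a pass. The exposure is up to 14 children per arm. Under a one-sided 95% Wald limit, two lost test-arm lesions change the verdict only near the margin; about the planned result six are needed, and the extreme case gives 15.0 points. The direction of any bias depends on who is lost, which the documents cannot tell us, so any bias size is illustrative. The documents do not support saying that the sample size is wrong, that the expected result is fragile to two children, or that Day 5 lesions are being misclassified. The change should be made, but the primary endpoint need not alter.

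**What to change.** In section 3.11 and the SAP, alongside the per-protocol analysis:

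1. Define both analysis sets. Add an analysis of CAL at 6-8 weeks in all randomised children, using the observed echo wherever there is one.
2. Where the 6-8 week Z scores are missing, multiply impute them within arm from the Day 5 Z scores, the 6-month Z scores where present, and baseline age, fever day and CRP. Derive CAL from the imputed Z scores by the section 3.4 definition. A Day 5 lesion serves only as a predictor and is not counted as CAL.
3. Name the non-inferiority interval and its confidence level, and add a tipping-point table showing how many missing test-arm children would need lesions for non-inferiority to be lost.
4. Show deaths before the 6-8 week echo as a sensitivity analysis, counted as CAL, without changing the primary endpoint.

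The cost is SAP wording and about a day of programming. Items 1 to 3 use data already on the CRF. Item 4 may need a death entry on the exit form and capture after discharge. The main limitation is that imputation assumes loss is explained by recorded data; the tipping-point table tests that assumption.

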### **3.7 Recruitment**

The clinical trial will be declared and registered at the ClinicalTrial.gov. Recruitment will be start after the protocol approved by the Institutional Review Board (IRB) at each sites of the participating institutions and will be ended in 2018 or until a total of 278 participants have been recruited.

### **3.8 Allocation**

Eligible participants will be randomized to either the IVIG alone or IVIG plus high-dose aspirin on an equal ratio. The investigator or his/her delegate will contact the Clinical Trial Center of Kaohsiung Chang Gung Memorial Hospital (KCGMH- CTC) after confirming that the patient fulfills all the inclusion/exclusion criteria. The KCGMH- CTC will assign a treatment arm to the patient. Randomization will use permuted blocks of random sizes. The block size will not be disclosed to ensure concealment.

### **3.9 Blinding**

Participants and study investigators are unblinded to the group of IVIG alone or IVIG plus high-dose aspirin.

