## **2.3 Trial design**

The trial is designed as a multi-center, prospective, randomized controlled, open-label, non-inferiority trial with two parallel groups to assess the efficacy of IVIG alone for the primary treatment in acute stage of KD. The primary endpoint is defined as the CAL formation at 6-8 weeks. Patients who meet the eligibility criteria are randomly assigned (1:1) to a test group (receiving IVIG alone) or a standard group (receiving IVIG plus high dose aspirin).

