### 3.4 Outcomes

#### Primary outcome

- **CAL**

The primary outcome is CAL at 6-8 weeks.

CAL will be evaluated by experienced pediatric cardiologists (at least 2 years experience of pediatric 2D echocardiography) using 2D echocardiography. The luminal diameter of left main coronary artery (LMCA) is measured at a point between the ostium and the first bifurcation of the artery (as Figure below). The luminal diameter of left anterior descending artery (LAD) is measured distal to and away from the bifurcation of the branch from the LCA. The luminal diameter of right coronary artery (RCA) is measured in the relatively straight section of the artery just after rightward turn from the initial anterior course of the artery. Definition of CAL is coronary artery luminal diameter greater than  $+3SD$  in one of the three proximal segments or greater than  $+2.5SD$  in two of the three proximal segments. The calculation of Z score is based on the website of Taiwan Society of Pediatric Cardiology ([http://www.tspc.org.tw/service/z\\_score.asp](http://www.tspc.org.tw/service/z_score.asp)).

[figure not shown]

**Figure:** coronary artery luminal diameter measurement in 2D echocardiogram

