| HGB  |       | g/dl       | RDW-CV     |       | %       | Basophil   |       | %    |
| HCT  |       | %          | PLT        |       | 1000/ul | AST/GOT    |       | U/L  |
| MCV  |       | fL         | Segment    |       | %       | ALT/GPT    |       | U/L  |
| MCH  |       | pg/cell    | Lymphocyte |       | %       | CRP        |       | mg/L |

**Week 6-8 follow up 2D echocardiography date:** 20□□/□□/□□ (yyyy/mm/dd)

Performer: \_\_\_\_\_

Body weight: □□.□ Kg

Body height: □□□.□ cm

LMCA: \_\_\_\_\_mm, Z score: \_\_\_\_\_

LAD: \_\_\_\_\_mm, Z score: \_\_\_\_\_

RCA: \_\_\_\_\_mm, Z score: \_\_\_\_\_

[figure not shown]

Coronary artery lesion: ☐Yes ☐No

Lesion type: \_\_\_\_\_

|                                                                                                                                                   |                                 |             |
|---------------------------------------------------------------------------------------------------------------------------------------------------|---------------------------------|-------------|
| I have reviewed all data recorded on all pages of this visit and certify that they are accurate, complete and consistent to the subject's record. | Investigator's Signature | Date |
|                                                                                                                                                   |                                 |             |

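### The primary endpoint is a reader-dependent echocardiographic measurement in an open-label trial, and the plan does not specify that the measuring cardiologist is masked to allocation; masking existing readers is a cheap improvement

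*Combined protocol and SAP*

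**What the plan says.** Section 2.3 describes a "randomized controlled, open-label, non-inferiority trial with two parallel groups". Section 3.9 (Blinding) consists of one statement: "Participants and study investigators are unblinded to the group of IVIG alone or IVIG plus high-dose aspirin".

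On the endpoint, section 3.4 says "The primary outcome is CAL at 6-8 weeks" and that "CAL will be evaluated by experienced pediatric cardiologists (at least 2 years experience of pediatric 2D echocardiography) using 2D echocardiography". The right coronary artery, for example, is "measured in the relatively straight section of the artery just after rightward turn". A lesion is defined as "coronary artery luminal diameter greater than $+3SD$ in one of the three proximal segments", or above +2.5SD in two of the three. Z scores come from one named online calculator.

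The CRF echo pages at day 5, week 6-8 and month 6 record the performer, weight, height, three diameters in mm and three Z scores, followed by a box "Coronary artery lesion: ☐Yes ☐No". No passage says whether the analysed endpoint comes from the box or from the recorded numbers.

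Under section 3.3, both arms take the same low-dose aspirin from the end of fever until 6-8 weeks.

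**The concern.** Open-label care does not require open-label outcome reading, but the plan does not draw that distinction. The reader chooses where to place the callipers within a described region, and the result is then dichotomised. A small change in a diameter near the cut-off therefore changes the child's outcome. As written, nothing prevents an unblinded investigator from measuring the primary endpoint.

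The study team has a stated expectation. Section 2.1 concludes from its own retrospective data that aspirin adds little to IVIG, and section 3.6 assumes less CAL without high-dose aspirin (15.4% against 17%). If that expectation influenced borderline readings in favour of the test arm, the trial would be more likely to declare non-inferiority wrongly. If the influence ran the other way, power would fall. A bias in the measured diameter cannot be removed later by re-analysing the recorded values.

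**Working it through.** **Inputs.** From section 3.6: CAL 17% (standard) and 15.4% (test), margin 10 points, alpha 0.05, power 80%, 125 per group, 139 after 10% dropout, 278 in total. From section 2.1: 35/341 = 10.3% CAL eight weeks after onset. The documents give no figure for reader error or reader bias, so every bias size below is an assumption.

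**1. The plan's own figure.** With unpooled variance and one-sided alpha 0.05 (section 3.6 does not state the sidedness):

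n = (1.645 + 0.842)² × (0.83×0.17 + 0.846×0.154) / (0.10 + 0.016)² = 124.7, so 125 per group. Then 125/0.9 = 138.9, so 139 per group and 278 in total. The figure reproduces. Masking the reader does not enter this formula, so the sample size is unchanged.

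**2. Illustration of a shift in readings.** Treat the measurement as one normal variable with a proportion p above the cut-off, and shift every reading in one arm down by s SD of the between-child distribution. With c = z(1−p), the fall in the CAL rate is p − P(Z > c + s).

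| Base rate p | c | s = 0.1 | s = 0.2 | s = 0.3 |
|---|---|---|---|---|
| 17% (section 3.6) | 0.954 | 2.4 points | 4.6 points | 6.5 points |
| 10.3% (section 2.1) | 1.265 | 1.7 points | 3.1 points | 4.4 points |

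Example: at p = 17% and s = 0.2, P(Z > 1.154) = 12.4%, and 17 − 12.4 = 4.6. Against the 10-point margin, a 0.2-SD shift uses about 46% at the higher base rate and about 31% at the lower one.

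**3. Effect on the conclusion.** Suppose the test arm is truly worse by exactly the margin (CAL 17% against 27%), with 125 per arm and one-sided alpha 0.05. A bias of b in favour of the test arm gives

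P(declare non-inferiority) = Φ(b/SE − 1.645), where SE = √[0.83×0.17/125 + (0.73+b)(0.27−b)/125].

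| Assumed bias b | 0 | 1 point | 2 points | 3 points | 5 points |
|---|---|---|---|---|---|
| False non-inferiority | 5.0% | 7.3% | 10.5% | 14.6% | 25.9% |

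One point is 1.25 children in an arm of 125. A bias of 3 or 5 points against the test arm, under the planned rates, would instead cut power from 80% to 55% or 38%.

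**4. Sensitivity to a single reading.** Take 21 lesions among 125 in the standard arm (17% of 125 is 21.25). The one-sided 95% upper bound for the excess CAL rate in the test arm is:

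- 23 lesions: 0.016 + 1.645×0.0482 = 9.5 points (non-inferior)
- 24 lesions: 0.024 + 1.645×0.0486 = 10.4 points (not non-inferior)

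Near the boundary, one reclassified child reverses the result. That is true of any binary endpoint; here it shows how small a reading effect could matter.

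**The case against.** Open-label conduct is a declared design choice, and the endpoint has a fixed numeric rule and one named calculator. Several stronger readings are tempting, but the documents do not support them.

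- **That the readers are unblinded.** Section 3.9 names participants and study investigators only. Section 3.4 assigns CAL to experienced pediatric cardiologists without saying that they are study investigators or know the arm. The plan is silent on them. The text of sections 1.5 and 3.1, listed in the contents, was not available, so the silence is judged on the rest.
- **That the tick box is the endpoint.** No passage says so. Diameters, Z scores, height and weight are recorded beside it, so the box can be checked. The box is therefore secondary, although the check would not reveal a biased diameter.
- **That this is the main source of bias.** Nothing in the documents ranks it. The primary analysis population, for one, differs between section 3.11 (per-protocol) and the statistical analysis text (intention-to-treat).
- **That masking is complete and free.** The common low-dose aspirin means that current treatment need not reveal the arm at 6-8 weeks. But families know the allocation, the CRF holds the randomization and high-dose aspirin pages alongside the echo pages, and the cost is not documented.
- **That the bias has a known size and direction.** The illustration shifts every child in one arm, which is stronger than moving only borderline readings, and uses one variable for a three-segment rule. The stated prior shows an expectation, not how a site cardiologist would measure.

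These points limit the wording and the size. They do not supply the missing safeguard.

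**Conclusion.** The point holds as an unspecified safeguard and a worthwhile, inexpensive improvement. The primary endpoint depends on the reader and on a threshold, investigators are unblinded, and the available text neither masks the measuring cardiologist nor separates that person from the treating team.

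The size of any bias is unknown. The illustrative range is 1.7 to 6.5 points across shifts of 0.1 to 0.3 SD and base rates of 10.3% and 17%, against a 10-point margin. It rests on assumed shifts, a normal distribution, and the same shift for every child in one arm. It shows that the matter is not negligible; it does not estimate what would happen. The 17% comes from retrospective data whose CAL time point the protocol does not give. The 10.3% rate is closer in timing to the endpoint, so the smaller figures deserve equal weight.

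**What to change.** Keep care open-label and add the following to sections 3.4 and 3.9:

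1. The 6-8-week and 6-month echocardiograms are requested under the trial number, without the arm.
2. They are measured by one of the existing cardiologists, who has no access to allocation. The echo page is kept apart from the allocation and treatment pages, and families are asked not to disclose the arm.
3. The CRF echo page gains a box to record any unblinding of the reader.

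As a secondary step, state that CAL is derived by program from the recorded diameters, height and weight, using the section 3.4 definition and its named Z-score calculator, rather than taken from the tick box. This removes discordant ticks but does not replace masked measurement.

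The cost is wording, a request form and a CRF box. The sample size stays at 125 per group, 139 with dropout and 278 in total, and no visit or extra reader is needed. The downside is that masking will be partial. A site where one cardiologist both treats and scans must swap the scan with a colleague or declare the reading unblinded.
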